### Safety reporting and trial oversight

All severe adverse events (SAEs) and suspected unexpected serious adverse reactions (SUSARs) are reported from the enrolment until 12-month follow-up. Persistent or significant disability or incapacity that was not expected with the given observed to expected lung to head ratio (O/E LHR) is evaluated as an SAE. An elective hospital admission is not a SAE. All SAEs and SUSARs are reported to the approving ethics committees in accordance with their requirements. We will report the SAEs and SUSARs that result in death or are life threatening within 7 days of first knowledge. All other SAEs and SUSARs will be reported within a period of maximum 15 days. Once a year throughout the clinical trial, we will submit a safety report to the approving ethics committees and competent authorities of the countries involved.

The trial will be monitored by qualified, independent monitors. The trial is classified as a trial with moderate risk and a specific monitoring plan is in place.

The data safety monitoring board will monitor the incidence of mortality on a continuous basis. If at some point a large difference in mortality, defined as an absolute risk increase of 25%, between the two treatment groups is noticed, the data safety monitoring board may recommend ending the study.

Insurance will cover compensation to patients who suffer harm from trial participation.

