## Introduction

Congenital diaphragmatic hernia (CDH) is a severe developmental defect of the diaphragm with an incidence of approximately 1 in 3000 live births and a mortality of 27%.^1^ Because of this defect, the abdominal organs herniate into the chest causing pulmonary hypoplasia and abnormal pulmonary vasculature growth, resulting in pulmonary hypertension (PH).^2^ In adults and children, PH is defined as mean pulmonary artery pressure (mPAP) exceeding 25 mm Hg with a pulmonary capillary wedge pressure of minimal 15 mm Hg.^3^

The normal pulmonary vascular transition of the neonate takes around 2 months to achieve these low values of mPAP. During fetal life, there is high resistance in the pulmonary circulation which results in most of the blood flow to bypass the lungs through the ductus arteriosus and oval foramen. Immediately after birth, the pulmonary vascular resistance drops and the blood flow to the lungs significantly increases.^4^ In contrast, the pulmonary vascular resistance often does not drop adequately in children with CDH due to a decreased vascular bed associated with lung hypoplasia, and an altered development of the pulmonary vasculature with excessive muscularisation of the arterioles, with increased thickness of the arterial media and adventitia. Although the presence of lung hypoplasia can be predicted with prenatal parameters, reliable predictors for PH in CDH patients are lacking.^5^ The incidence of PH in CDH patients is 68%–79% and causes considerable morbidity and mortality.^1 2 6^ Therapy in newborns with PH, such as inhaled nitric oxide (iNO) and sildenafil, has improved outcomes in general. However, trials in infants with CDH are sparse.

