### Sample size calculation

The sample size calculation is based on a power analysis for the primary outcome, using previously published data on PH. Lusk *et al* showed that PH, defined as >2/3 systemic blood pressure measured on echocardiography, in CDH patients on day 14 has a positive predictive value of 0.8 for death, death or ventilation, and death or ventilator support. PH on day 14 is observed in 64% of CDH patients.^24^

Even though the definition of the primary outcome is not the same, we assume a similar outcome percentage of 64% for failing the primary outcome in our trial, the absence of PH on day 14 without pulmonary vasodilator therapy and/or absence of death within the first 28 days of life, in the iNO group. Our aim is to promote practice change; therefore, we aim for a clinically significant difference. For a 25% relative reduction to 48%, a sample size of 300 patients (150 patients per group) is needed to obtain a power of 80%. This will match a number needed to treat of 6.25. Taking missing data and the effects of correction for covariates into account, we adjust this sample size to 330 patients. In the collaborating centres 550 patients will be born in 3 years. Based on our earlier trial (CMV Versus HFO in Congenital Diaphragmatic Hernia; VICI trial) we expect to have an inclusion rate of 60%. Therefore, the inclusion of 330 patients should be reached in 3 years.

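### The advisory mortality trigger for the data safety monitoring board is a constant 25 points whatever the number of infants observed; it is easily crossed by chance at small numbers and insensitive to a 10–15 point excess later

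*Protocol article*

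**What the plan says.** The rule is in the protocol article under Safety reporting and trial oversight. On timing: "The data safety monitoring board will monitor the incidence of mortality on a continuous basis". The condition is that, at some point, "a large difference in mortality, defined as an absolute risk increase of 25%, between the two treatment groups is noticed", and the consequence is that "the data safety monitoring board may recommend ending the study".

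Three features are therefore fixed in the text: monitoring is continuous, the condition can be met at any time, and the threshold is one number. It is not tied to a count of infants or deaths, or to a measure of precision. The consequence is advisory. The article does not say whether the increase counts only against sildenafil or against either arm, so both are given below. It states no other criterion for a mortality difference.

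**The concern.** The standard error of a difference between two proportions shrinks with the square root of the sample size. A constant difference is therefore a weak criterion when few infants are in and a very strict one when many are. A board using the published number would get alerts early that chance often explains, and no alert later at excesses in mortality that the data could by then distinguish from chance.

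The trial's own scale makes the later problem plain. The sample size section treats a 16-point difference (64% − 48%) in a composite that includes death as clinically significant and enough to change practice. An excess of that size in deaths alone would fall short of what the oversight section calls a large difference. What is at stake is the usefulness of the only quantitative mortality guide that the article gives the board, in newborns with high background mortality.

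**Working it through.** **Inputs.**
- Threshold: 25 points, constant (Safety reporting and trial oversight).
- Timing: the board "will monitor the incidence of mortality on a continuous basis"; no first look is stated, so several start points are shown.
- Control mortality: the Introduction gives CDH "a mortality of 27" per cent. That covers all CDH infants, whereas the trial enrols those with pulmonary hypertension, so 20% to 40% is used as an assumed range.
- Size: the Sample size calculation section says "we adjust this sample size to 330 patients", i.e. 165 per arm. The base figure reproduces: 64% against 48%, two-sided 0.05 and 80% power give 150 per group, and 300 × 1.10 = 330.

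The article states no error rate for the trigger, so there is no trigger figure to reproduce.

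**Step 1. What 25 points means at each sample size.** For 27% against 52%, the pooled proportion is (0.27 + 0.52)/2 = 0.395. Then SE = √(2 × 0.395 × 0.605 / n) and z = 0.25 / SE.

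| Infants per arm | SE | z |
|---|---|---|
| 10 | 0.219 | 1.14 |
| 20 | 0.155 | 1.62 |
| 30 | 0.126 | 1.98 |
| 50 | 0.098 | 2.56 |
| 100 | 0.069 | 3.62 |
| 165 | 0.054 | 4.65 |

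At 165 per arm the trigger is 0.25 × 165 ≈ 41 excess deaths. A true 15-point excess is 0.15 × 165 ≈ 25 excess deaths; an ordinary two-sided 0.05 test at that size has 82% power for it.

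**Step 2. Chance of crossing under continuous looks.** Simulated trials accrue 1:1 to 165 per arm. The observed difference is checked after each pair from the stated start, and outcomes are treated as known at once. Control mortality is 27%. False and true crossings are shown for the same start point.

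| First look (per arm) | No true difference: one direction / either | True +15 points |
|---|---|---|
| 10 | 18% / 36% | 60% |
| 20 | 7% / 14% | 48% |
| 30 | about 2.5% / 5% | 38% |
| 50 | 0.4% / 0.8% | 27% |

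From 50 per arm, a true +10 points crosses in 10% of trials and +20 points in 54%.

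Over 20% to 40% control mortality, the false-crossing rate from 10 per arm runs from 14%/28% to 22%/45%. The crossing rate for +15 points from 50 per arm runs from 24% to 29%.

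**Step 3. Comparison with a boundary that depends on information.** Five looks at 33, 66, 99, 132 and 165 per arm, control mortality 27%, pooled z statistic. The Pocock-type boundary is z ≥ 2.413 at each look. The O'Brien-Fleming type is z ≥ 2.040 × √(5/k) at look k.

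| Rule | False flag, one direction | +10 | +15 | +20 |
|---|---|---|---|---|
| Constant 25 points | 0.8–0.9% | 10% | 24% | 48% |
| Pocock-type | about 2.5% | 40% | 73% | 93% |
| O'Brien-Fleming type | about 2.5% | 49% | 81% | 96% |

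The constant rule ranks last at 20% and 40% control mortality too. Solving d = z × √(2p(1 − p)/n) with p = 0.27 + d/2 shows why. The Pocock-type boundary asks for about 29 points at 33 per arm but only about 12.5 at 165; the O'Brien-Fleming type asks for about 56 and then 10.5.

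**The case against.** The strongest reply is that this is not a stopping rule. The board may recommend ending the study; crossing obliges nothing, and nothing bars it from acting below 25 points. It sees mortality continuously, and fatal or life-threatening events go to ethics committees within 7 days. This stands. Every percentage here is a chance of crossing a line, and a 15-point excess would not be invisible to the board.

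A reader might infer that the trigger both fires by chance early and is almost blind to serious harm later. The article does not support that. No single start point shows both faults at full strength: looks from 10 per arm give the 18% false-crossing rate but cross in 60% of trials under +15 points, whereas looks from 50 per arm miss most +15-point excesses but have almost no false crossings. Nor does blindness describe +20 points, which looks from 50 per arm catch about half the time.

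The five-look comparison also deserves caution. It restricts a rule meant for continuous use, and the false-flag rates are unequal (0.8–0.9% against about 2.5%), so part of the gap reflects those choices. Most of it would remain: with continuous looks from 30 per arm, where the false-crossing rate is about 2.5%, +15 points is still crossed in only 38%.

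Finally, a board charter or the full protocol V.4 may set a first look or a boundary. Neither is shown, and the absence of such detail is not the point. The published definition is a stated constant, and a charter rule that differed from it would have to be reconciled with it.

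**Conclusion.** The point holds in a limited form. The constant 25-point trigger is a poor guide because its meaning shifts from about 1.1 standard errors at 10 infants per arm to about 4.65 at 165. Starting early buys sensitivity at the price of frequent chance crossings. Once about 50 or more per arm are in, the trigger is insensitive to a true excess of 10–15 points (10% and 27%) and catches +20 points about half the time.

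The figures rest on 27% control mortality (same pattern over 20–40%), equal accrual to 165 per arm, immediate knowledge of outcome and an assumed first look. They do not show that the trial would be stopped wrongly or that harm would go unnoticed, because the trigger is advisory. The primary analysis and sample size are untouched. It should be fixed, but does not by itself undermine the trial.

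**What to change.** Keep the continuous mortality review and the board's discretion. Replace the constant 25-point definition, or supplement it, with a non-binding harm boundary on mortality that depends on the information accrued. One workable choice is Lan-DeMets spending with one-sided 0.025 per direction at about five formal looks: Pocock-type, or O'Brien-Fleming type if early chance alarms are the main worry. State whether the boundary applies to excess deaths in either arm or only under sildenafil, and that crossing it prompts a board judgement.

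The cost is wording in the protocol and the board's charter, and about a 2.5% chance per direction of a false harm flag. No extra infants or procedures are needed. No primary-endpoint alpha is spent, provided that a crossing is treated as a safety signal and not as an efficacy result.

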## Ethics and dissemination

The trial will be submitted to the regulatory bodies and the local institutional review boards (IRB) in all participating countries. Important amendments will be communicated to all relevant parties. The study will be conducted according to the principles of the Declaration of Helsinki, in accordance with the Medical Research Involving Human Subjects Act and national rules and regulations on personal data protection. Parental informed consent will be obtained. The results of this study will be disseminated via peer-reviewed publications and implemented in the international guidelines for the treatment of newborns with CDH.
